### Determination of alternative labels to be tested

We undertook a targeted literature search in May 2023 by retrieving forward and backward citations of three key papers that considered low-risk prostate lesions and cancer labelling.^21 24^ We used an automated tool ‘Spidercite’^37^ to identify records, and Covidence to screen title, abstract and full-texts (Veritas Health Innovation, Australia; https://www.covidence.org). Of 362 unique records retrieved, we screened the full text of 44 and included 9 papers describing 7 alternative labels for prostate cancer (table 1). Using short online questionnaires implemented in Qualtrics (Provo, Utah, USA: Qualtrics, 2020), we ran two rounds of survey with the eight international clinician investigators (with expertise in prostate pathology, primary care, urology and radiation oncology) and four consumer investigators (two with lived experience of low-risk prostate cancer and two without a history of prostate cancer) to determine choice of alternative labels we would test in the online survey. In the first-round surveys, clinician and consumer investigators ranked the seven labels identified in the targeted literature search and an additional label ‘low-risk prostate lesion’ in order of preference. Both clinicians and consumers highly ranked ‘low-risk prostate lesion’, and this was chosen as one of the alternative labels to be tested. Clinicians also highly ranked IDLE and PAN-LMP, and one clinician suggested a new label ‘low-risk neoplasm’. In the second-round survey, in which clinicians and consumers considered these three alternative labels, ‘low-risk prostate neoplasm’ was ranked highest by both groups and so was chosen as the second alternative label to be tested.

**Table 1 T1:** Studies that considered alternatives to low-risk prostate cancer

Authors (year)	Study type	Participants	Labels included
Berlin *et al* (2023)^30^	Discrete choice experiment	1254	Adenocarcinoma, acinar neoplasm, prostatic acinar neoplasm of low malignant potential, prostatic acinar neoplasm of uncertain malignant potential, neoplasm, tumour, growth.
Zhou *et al* (2023)^45^	Comment	NA	Non-cancer.
Eggener *et al* (2022)^46^	Editorial	NA	Indolent lesion of epithelial origin.
Epstein (2022)^47^	Editorial	NA	Indolent lesion of epithelial origin.
Hudnall *et al* (2021)^29^	Online survey	748	Gleason 6 out of 10 prostate cancer, grade Group 1 out of 5 prostate cancer, indolent lesion of epithelial origin.
Ho *et al* (2019)^48^	Review	NA	Indolent lesion of epithelial origin.
Varma (2018)^49^	Comment	NA	Indolent lesion of low malignant potential, tumour of uncertain malignant potential.
Epstein (2018)^50^	Editorial	NA	Indolent lesion of epithelial origin.
Epstein *et al* (2016)^51^	Review	NA	Indolent lesion of epithelial origin.
Kulac *et al* (2015)^52^	Editorial	NA	Indolent lesion of epithelial origin.

### Sample size

Separate calculations were done for the required sample sizes for the studies of men and women with male partners. We estimated a sample size of 1290 participants with 430 participants per group in the study of men, and 1410 participants with 470 participants per group in the study of women with male partners, would each provide 80% power to detect a pairwise difference in the absolute proportion choosing conservative management as small as 10%.

The assumptions are: 70% of men with a prostate^30 39^ and 65% of women with male partners^30^ would choose conservative management in the control label condition, a 5% dropout rate, α=0.05, the normal approximation to the binomial distribution and the standard formula for comparing proportions in independent equal-sized groups.^40^

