**Methods and analysis:**

We will run two separate studies for Australian men and Australian women with a male partner. Both studies are between-subjects factorial (3×2) randomised online hypothetical experiments. Following consent, eligible participants will be randomised 1:1:1 to three labels: ‘low-risk prostate cancer, Gleason Group 1’, ‘low-risk prostate neoplasm’ or ‘low-risk prostate lesion’. Participants will then undergo a second randomisation step with 1:1 allocation to the provision of detailed information on the benefits and harms of different management choices versus the provision of less detailed information about management choices. The required sample sizes are 1290 men and 1410 women. The primary outcome is the participant choice of their preferred management strategy: no immediate treatment (prostate-specific antigen (PSA)-based monitoring or active surveillance using PSA, MRI, biopsy with delayed treatment for disease progression) versus immediate treatment (prostatectomy or radiation therapy). Secondary outcomes include preferred management choice (from the four options listed above), diagnosis anxiety, management choice anxiety and management choice at a later time point (for participants who initially choose a monitoring strategy).

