### Analysis

The two studies (men and women) will be run in parallel and analysed separately. Each study will include variables used in sampling strata: age, education and geographical location (by state/territory). All analyses will adhere to the intention-to-treat principle, with participant data analysed according to the randomly assigned study arm, regardless of adherence to the study protocol. We will present categorical data using counts and percentages, and continuous data using the minimum and maximum, mean and SD or median and quartile 1 (Q1) and quartile 3 (Q3). For each outcome, we will present the number of participant responses included in the analysis.

Statistical analyses will use a superiority framework to make pairwise comparisons across the three label groups. We will use logistic regression for binary outcomes and linear regression for continuous outcomes. We will present 95% CIs for effect estimates on all primary and secondary outcomes. As well as the effects of the alternative diagnostic labels, we will estimate the effects of the provision of absolute risk information. We will investigate effect modification of the label effects by provision of absolute risk information through testing significance of interaction terms with the label group variable. All hypothesis tests will be two-sided with an α of 5%. P values from secondary analyses will not be adjusted for multiple testing and so will be interpreted conservatively.

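### The stated 430 men and 470 women per label group do not follow from the stated α, power, difference and dropout, which leaves the α per primary comparison unclear

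*Protocol article*

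**What the plan says.** The Sample size section of the protocol article gives 430 per label group (1290 in total) for men and 470 per label group (1410 in total) for women, and says these "would each provide 80% power to detect a pairwise difference in the absolute proportion choosing conservative management as small as 10" percentage points.

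The same section lists the assumptions:
- Control rate: "70% of men with a prostate", and 65% of women with male partners, "would choose conservative management in the control label condition".
- Dropout, error rate and approximation: "a 5% dropout rate, α=0.05, the normal approximation to the binomial distribution".
- Method: "the standard formula for comparing proportions in independent equal-sized groups".

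The Abstract says that "eligible participants will be randomised 1:1:1 to three labels" and calls 1290 and 1410 the required sizes.

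The Analysis section plans pairwise comparisons across the three label groups and states: "All hypothesis tests will be two-sided with an α of 5" per cent. It says that secondary P values will not be adjusted for multiplicity. It does not say whether the three primary comparisons will be.

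**The concern.** Every input to a two-proportion calculation is on the page, so the sizes should be reproducible. They are well above what the inputs give, in both studies and by a similar proportion. That pattern suggests that the calculation used an assumption the text does not report.

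The most natural candidates are a smaller α for each of three pairwise comparisons, or a higher power. Which one it was matters for the primary analysis. A primary P value between 0.0167 and 0.05 counts as significant if each comparison is tested at 5%, and does not if 5% is split over three. The sample size paragraph is where a reader would look to settle this, and its numbers do not agree with its own stated α and power.

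**Working it through.** **Inputs** (Sample size section unless noted): control rate p1 = 0.70 (men) and 0.65 (women); difference 0.10; power 80%; α = 0.05, two-sided (Analysis section); dropout 5%; equal groups.

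**Attempt to reproduce the stated sizes.** Pooled normal-approximation formula, with p̄ = (p1+p2)/2:

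n = [z(1−α/2)·√(2p̄(1−p̄)) + z(power)·√(p1(1−p1)+p2(1−p2))]² / (p1−p2)², then divide by 0.95.

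- Men, 70% vs 80%: (1.960×√0.375 + 0.8416×√0.37)² / 0.01 = (1.2002 + 0.5119)² / 0.01 ≈ 293.2; /0.95 = 308.6, about 309. Stated: 430.
- Women, 65% vs 75%: (1.960×√0.42 + 0.8416×√0.415)² / 0.01 = (1.2702 + 0.5422)² / 0.01 ≈ 328.5; /0.95 = 345.8, about 346. Stated: 470.

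Ratios: 430/308.6 = 1.39 and 470/345.8 = 1.36. The stated sizes are not reproduced.

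**Standard variants at two-sided α=0.05 and 80% power**, per group after dropout:

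| Variant | Men | Women |
|---|---|---|
| Unpooled variance, increase | 305.7 | 342.9 |
| Pooled, increase | 308.6 | 345.8 |
| Pooled with continuity correction, increase | 329.3 | 366.5 |
| Pooled, decrease (70→60, 65→55) | 374.7 | 395.3 |
| Pooled with continuity correction, decrease | 395.4 | 416.1 |
| **Stated** | **430** | **470** |

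A one-sided test needs fewer still. None reaches the stated sizes.

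**What would come close** (increase of 10 points, pooled, after dropout):

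| Assumption | Men | Women |
|---|---|---|
| α=0.05/3=0.0167, 80% power | 411.8 | 461.4 |
| α=0.05, 90% power | 412.6 | 462.3 |
| α=0.025, 85% power | 422.3 | 473.2 |
| First row with continuity correction | 432.6 | 482.2 |
| Second row with continuity correction | 433.4 | 483.2 |

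None returns exactly 430 and 470, and the first two rows cannot be told apart. If α=0.05 and 80% power are both kept, dropout would have to be 1−293.2/430 = 32% (men) and 1−328.5/470 = 30% (women), or the detectable increase about 8.6 points in each study. Each of these contradicts a stated input.

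**Power that the stated sizes give.** After 5% dropout: 430×0.95 = 408.5 and 470×0.95 = 446.5 per group.

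Power = Φ{[0.10·√n − z(1−α/2)·√(2p̄(1−p̄))] / √(p1(1−p1)+p2(1−p2))}.

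Men, increase, α=0.05: (2.0211 − 1.2002)/0.6083 = 1.350, so 91.1%. Women: (2.1131 − 1.2702)/0.6442 = 1.308, so 90.5%.

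| Comparison | α=0.05 | α=0.0167 |
|---|---|---|
| Men, 70→80% | 91.1% | 81.9% |
| Women, 65→75% | 90.5% | 80.8% |
| Men, 70→60% | 85.1% | 72.8% |
| Women, 65→55% | 86.3% | 74.5% |

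**The case against.** The strongest defence is that α=0.05 is the familywise level. The Analysis section exempts only secondary P values from adjustment, which suggests that the primary comparisons may be adjusted. Splitting 0.05 over three comparisons gives about 412 and 461 per group at 80% power, close to the stated sizes, and then neither the stated α nor the stated power is false. What is missing is the split, and a condensed article may leave such detail to the full protocol or the analysis plan. This stands far enough that one cannot say flatly that either the stated power or the stated α is wrong. It does not remove the point. The same section sets 5% for all tests, and the Sample size section puts α=0.05 beside sizes that do not follow from it. The text is inconsistent, not merely brief.

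The second defence is that the discrepancy is conservative. That also stands: at α=0.05 the sizes more than meet 80% power for a rise and for a fall.

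Two stronger readings are tempting and should be resisted:
- A reader might infer that a Bonferroni α of 0.0167 was used. The numbers fit 90% power at α=0.05 equally well, and the document states neither.
- A reader might infer that the trial is underpowered for a fall of 10 points, since the tests are two-sided and the Introduction reports an experiment in which a non-cancer label fared worse than a Gleason Group 1 cancer label. The shortfall (72.8% and 74.5%) arises only at α=0.0167, which the document never gives. The non-cancer label in that experiment is also not one of the labels tested here.

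**Conclusion.** The point holds as an error in a stated figure. With the rates, difference and dropout as written, two-sided α=0.05 per comparison and 80% power cannot both be the values behind 430 and 470. The sizes exceed the requirement by 39% (men) and 36% (women). If α=0.05 applies to each comparison, the power is about 91% and 90%, not 80%.

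This is not a power shortfall. Its consequence is that the α for each primary pairwise comparison is left uncertain, which needs settling before the primary results are interpreted. The conclusion rests on the normal approximation and on 5% dropout applied as division by 0.95. The choice among pooled, unpooled and continuity-corrected forms does not alter it. Which unreported assumption produced the sizes cannot be established from the document.

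**What to change.** Keep the sample sizes and state the per-comparison α and the power actually used.

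- If 0.05 is the familywise level over three pairwise comparisons: write two-sided α=0.0167 per comparison with 80% power for a 10-point increase over control, and have the primary comparisons in the Analysis section use that α. The 80% claim should then be limited to an increase.
- If α=0.05 applies to each comparison: restate the power as about 91% (men) and 90% (women) for a 10-point increase. Power for a 10-point decrease is then also above 80%, so no limit on direction is needed.

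If some other input was used, report that input instead. The cost is a few words in the Sample size section and, under the first option, one sentence in the Analysis section. No extra participants are needed.

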### Analysis

The two studies (men and women) will be run in parallel and analysed separately. Each study will include variables used in sampling strata: age, education and geographical location (by state/territory). All analyses will adhere to the intention-to-treat principle, with participant data analysed according to the randomly assigned study arm, regardless of adherence to the study protocol. We will present categorical data using counts and percentages, and continuous data using the minimum and maximum, mean and SD or median and quartile 1 (Q1) and quartile 3 (Q3). For each outcome, we will present the number of participant responses included in the analysis.

Statistical analyses will use a superiority framework to make pairwise comparisons across the three label groups. We will use logistic regression for binary outcomes and linear regression for continuous outcomes. We will present 95% CIs for effect estimates on all primary and secondary outcomes. As well as the effects of the alternative diagnostic labels, we will estimate the effects of the provision of absolute risk information. We will investigate effect modification of the label effects by provision of absolute risk information through testing significance of interaction terms with the label group variable. All hypothesis tests will be two-sided with an α of 5%. P values from secondary analyses will not be adjusted for multiple testing and so will be interpreted conservatively.

We will estimate unadjusted and adjusted effects using the relevant regression model, and will present these across important patient characteristics including: age, state or territory, relative socioeconomic disadvantage (postcode-based), remoteness (postcode-based), education, language spoken at home, family member with prostate cancer diagnosis and other participant characteristics in table 2. For the adjusted analyses, we will include baseline measurements of important prognostic factors for the outcome in the model, which is recommended to improve the power of the study^41^ and to obtain valid SEs when using stratification.^42^ These will include variables used in sampling strata: age, education and geographical location (by state/territory). Other prognostic factors will be measured through the baseline questionnaire, and include baseline anxiety levels, prior diagnosis of (non-prostate) cancer, diagnosis of prostate cancer in a family member or close friend. The effects of participants’ health literacy on intervention effects will also be explored as a potential confounder. Data analysis will be conducted in R V.4.3.2.^43^

### Patient and public involvement

Four consumer investigators are involved in this research. As well as providing valuable input into the choice of alternative labels, they have reviewed study materials to ensure these are optimum for the community samples we will recruit. The research question and outcome measures were informed by patient experiences of overdiagnosis and harm related to low-risk prostate cancers.^44^ Patients and the public will not be directly involved in the recruitment and conduct of the study. We aim to share a lay summary of the study findings with health consumer groups for dissemination in the wider community.

### Planned start and end dates for the study

The anticipated date of first participant enrolment was 01 April 2024 and the anticipated date of last data collection completion was 30 April 2024 (see Australian New Zealand Clinical Trials Registry entries ID 386701 and 386889).

### Ethics and dissemination

Ethics approval for this study was obtained by the University of Sydney’s Human Research Ethics Committee on 21 September 2023 (Project Number 2023/572). This study has been created as a project on the Open Science Framework (OSF) Platform (https://doi.org/10.17605/OSF.IO/UN9GB). Updates to the protocol will be uploaded to the OSF platform and identified by version number. The two trials are registered with the Australian New Zealand Clinical Trials Registry. Updates to the protocol will also be uploaded to the registry and identified by version number.

As this study is an online randomised experiment that includes a hypothetical survey, we do not anticipate significant adverse events because of the trial interventions or conduct. Participants are reminded at several points before and after the study as part of the participant information, consent and debrief processes that the nature of the study is hypothetical, that none of the information relates to their actual health or well-being and that researchers do not have access to their actual medical histories or information. The debriefing content also includes links to relevant resources for participants who wish to find out more.

The research team will have access to the final trial data set. Access may be granted to other researchers on reasonable request. No contractual agreements limit the disclosure of data to other investigators.

The findings of the study will be published in a peer-reviewed medical journal. A lay summary of the findings will be published via the permanent link at the Wiser Healthcare publications page. This research will provide robust evidence on the potential effects of proposed changes to the terminology of low-risk prostate lesions on uptake of, and persistence with, active surveillance. It may inform policy discussion, public health approaches and medical guidelines regarding which prostate lesions have a cancer label. It may also help to inform clinician practice regarding how clinicians discuss prostate cancer, its risks and management options.
